### Outcome measurements

The variables of this trial include basic characteristics, primary and secondary outcomes, and exploratory results. The basic characteristics will be determined from a questionnaire administered at baseline (1–2 weeks before randomization). The primary and secondary outcomes will be measured at baseline and at the end of the intervention (4 weeks after randomization). The exploratory results will be measured at baseline and at the end of the intervention (4 weeks after randomization). All results will be assessed by experienced assessors who do not know the group assignments of the participants.

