### fNIRS-EEG-EMG experimental paradigm

There will be three tasks: upper limb forward reach, elbow flexion and extension, and Tai Chi Yunshou. After a 3-min rest period (baseline), the motor paradigm will use a three block design:Upper limb forward reach with three cycles of preparation [3 s] – reach forward [3 s] – rest [3 s];Elbow flexion and extension with three cycles of preparation [3 s] – elbow flexion [3 s] – rest [3 s] – elbow extension [3 s] – rest [3 s];Tai Chi Yunshou with three cycles of preparation [3 s] – Tai Chi Yunshou [3 s] – rest [3 s]

For each motor task, there will be 3 s of preparation. The subjects will be asked to perform specific motor tasks for 3 s according to the instructions and then relax for 3 s. Each motor task will consist of 20 repetitions. The tests will be carried out on both sides of the arm of post-stroke patients. Each subject will use his/her left and right hands to perform each motor task. He/she will take a 5-min break between each task to prevent muscle fatigue. The experiment will last for 30 min for each subject (2 hands × 3 tasks × 20 repetitions). Finally, the static state will be assessed for 3 min. Data will be collected at baseline and after the 4-week intervention.

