Effective connectivity (EC) analysis of the CLN is based on defining brain and muscle regions and ROIs. The basis for extracting ROIs from brain regions is that the brain map guides ROIs, and there are no overlapping regions to ensure the selection of functionally meaningful connected regions. The cortical reconstruction of the head model is used as the accurate geometric head model of the subjects. The EEG signals collected from the standard electrode leads of the international 10–20 system are represented on an accurate geometric model. First, the motor areas of the unaffected and affected sides are selected as ROIs, defined as Mu and Ma, respectively. The unaffected and affected somatosensory cortices are also considered to be ROIs, corresponding to Su and Sa, respectively. Finally, ROIs from unaffected and affected frontal and parietal regions are defined as Fu, FA, PAu, and PAa, respectively. For the muscle regions related to the two anatomical parts of the upper limb, according to the signals collected from the myoelectric electrodes on the affected side, the proximal (including the superior trapezius, the anterior deltoid, the posterior deltoid, the middle deltoid, the biceps brachii and the triceps brachii) and distal muscles (including the flexor carpi radialis and the extensor carpi radialis longus) of the upper limb are divided into two regions, which are defined as PM and DM. Based on the above 14 ROIs, the inflow index (IFI) and the outflow index (OFI) are used to determine the causal relationship between ROIs before and after training. To determine the difference in the average FcePDC value between the two groups in each frequency band before and after training, the FcePDC value calculated before training is defined as the baseline. The baseline changes are calculated by subtracting the baseline before training from the post-training values, and an independent-sample two-tailed *t*-test is performed to compare the changes between the two groups. In addition, repeated measures analysis of variance is used to test the statistical difference in the average FcePDC values in different information flow directions before and after training. Bonferroni correction is used to correct for multiple comparisons. The inter-group differences in network parameters (weighted clustering coefficient [C_W_] and weighted shortest path length [L_W_]) are tested with the Mann-Whitney *U* test. For EC analysis, the IFI and OFI values of ROI changes before and after training in the two groups are tested by paired two-tailed *t*-tests. The consistently paired *t*-test is used for the betweenness centrality parameter (BCX). The confidence level *α* is defined as 0.05.

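### The between-arm tests of FcePDC, C_W and L_W are valid, but they give up precision by not using the recorded pre-training value as a covariate, and the Mann-Whitney response is not stated

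*Protocol article*

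**What the plan says.** The mechanism outcomes have their own tests in the protocol article, under Analysis of fNIRS, EEG, and EMG data.

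- **FcePDC.** The pre-training value serves as baseline and is removed by subtraction: "The baseline changes are calculated by subtracting the baseline before training from the post-training values". The test applied to that difference has no covariate: "an independent-sample two-tailed *t*-test is performed to compare the changes between the two groups".
- **C_W and L_W.** "The inter-group differences in network parameters (weighted clustering coefficient [C_W_] and weighted shortest path length [L_W_]) are tested with the Mann-Whitney *U* test". The sentence does not say which quantity is ranked.
- **Error rate.** "Bonferroni correction is used to correct for multiple comparisons", with no count of comparisons. Alpha "is defined as 0.05".

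The pre-training value is available for all of them. The section on the fNIRS-EEG-EMG experimental paradigm states: "Data will be collected at baseline and after the 4-week intervention". Outcome measurements repeats this schedule for the exploratory results.

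Nothing else in the article supplies the missing covariate. The mixed model and the age, gender and BMI covariates belong to the behavioural indicators. The adjustment at the end of the mechanism section belongs to the correlation analysis and does not name the pre-training value.

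**The concern.** A raw change score fixes the slope of the post value on the pre value at 1. If the true slope is smaller, subtraction adds noise. With equal variances and rho below 0.5, the change is noisier than the post value alone. A rank test on post values has the opposite weakness: it discards the pre-training value, which costs most when that value predicts the outcome well. Regression on the pre-training value estimates the slope from the data. Apart from one degree of freedom, it is never less efficient than either.

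The neural mechanism is the second stated aim of the trial, and these comparisons are randomised evidence on it. No power is stated for them, so there is no declared margin to absorb a loss. What is at stake is a real between-arm difference being missed.

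**Working it through.** **The plan's own figure.** No power or effect size is given for FcePDC, C_W or L_W. The only effect size is the one for FMA-UE under Sample size estimation: (60.50 − 59.14) / sqrt((2.19² + 1.77²)/2) = 1.36 / sqrt(3.9645) = 1.36 / 1.991 = 0.683. This reproduces the stated 0.6830377. The stated 64 evaluable does not follow from it: a two-sided t-test needs 35 per arm (70), and 32 per arm gives 76.7% power. That is a separate matter; only the effect size is borrowed here.

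**Inputs.** From the document: d = 0.683 (borrowed), alpha 0.05, a two-tailed test (stated for FcePDC), 84 randomised and 20% dropout, so 84 × 0.8 = 67.2, taken as 34 + 33. Assumed: rho of 0.3, 0.5 and 0.7, equal pre and post variance, normality, and an arm effect measured in post-value SDs.

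**Variance of each comparison** (post variance = 1):

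- change score: 2(1 − rho), which is 1.40, 1.00, 0.60
- post value alone: 1
- adjusted for the pre value: 1 − rho², which is 0.91, 0.75, 0.51

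The ratio of adjusted to change-score variance is (1 + rho)/2 = 0.65, 0.75, 0.85. Adjustment therefore cuts the variance by 35%, 25% and 15%.

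**Power.** Divide 0.683 by the square root of the variance, then multiply by sqrt(34 × 33/67) = 4.092 to get the noncentrality of a t-test on 65 df (64 with the covariate). For Mann-Whitney, also multiply by sqrt(3/π) = 0.977 (efficiency 0.955 under normality). Points lost against the adjusted linear model are in brackets, taken before rounding.

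| rho | Adjusted linear model | t-test on change | Mann-Whitney on post | Mann-Whitney on change |
|---|---|---|---|---|
| 0.3 | 82.3% | 64.3% (17.9) | 76.8% (5.5) | 62.3% (19.9) |
| 0.5 | 88.9% | 78.6% (10.2) | 76.8% (12.1) | 76.8% (12.1) |
| 0.7 | 97.1% | 94.5% (2.6) | 76.8% (20.3) | 93.5% (3.6) |

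The two readings of the Mann-Whitney test cost the same at rho 0.5 and move in opposite directions on either side of it.

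**Simulation check** (5,000 runs, 32 per arm, rho 0.5): t-test on change 74.9%, adjusted model 85.6%, Mann-Whitney on post 73.6%, on change 72.9%. The gap between the first two is 10.7 points, the same as the formula gives at that size (76.7% against 87.4%).

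**Sensitivity of the change-score loss at rho 0.5.**

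- Effect size, 32 per arm: 2.5 points at d = 0.2, 9.3 at 0.4, 11.9 at 0.5, 7.0 at 0.8, 1.9 at 1.0.
- Evaluable number, d = 0.683: 10.7 points at 32 per arm, 9.8 at 35, 7.5 at 42.
- Bonferroni for 3 to 10 tests, 32 per arm, d = 0.683: 14.5 to 16.1 points.

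**The case against.** The strongest reply is that nothing here is an error. Under randomisation both planned tests hold their type I error, the outcomes are labelled exploratory, the sample size rests on FMA-UE alone, and no power is claimed for the mechanism measures. All of that stands. It makes this a matter of efficiency, and it rules out calling the results biased. A reader might infer that chance pre-training imbalance would produce false differences. Such results are already counted within the nominal alpha.

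Three further replies stand in part.

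- The FcePDC test does use the pre-training value, by subtraction. A reader might infer that it is ignored; the accurate statement is that it is not a covariate.
- The Mann-Whitney response is open. The article speaks of dynamic changes before and after Tai Chi when it introduces the network analysis, so ranked changes are as plausible as ranked post values. Both are therefore shown above, and at the assumed values both lose power against the adjusted model.
- The correlation analysis selects brain regions that differ between groups. C_W and L_W describe the whole network and FcePDC is tested as a band average, so it is uncertain that these contrasts drive that selection.

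The reply that this can wait for the statistical analysis plan is weaker. The article states the tests themselves; the point is about what it fixes, not about a detail it leaves out.

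**Conclusion.** The point holds as a loss of precision on exploratory outcomes that can be avoided at almost no cost. Under the stated assumptions the change-score test for FcePDC loses about 18, 10 and 3 points of power at rho 0.3, 0.5 and 0.7. Mann-Whitney on post values loses about 5, 12 and 20; on changes it follows the change-score pattern.

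Two stronger readings are not supported. The first is that low repeatability makes the loss worse for all three measures. That is true of change scores only and reverses if post values are ranked. The second is that 10 points is a property of this plan. It is one scenario, with an assumed rho, equal variances and an effect size borrowed from another outcome. It shrinks for very small or large effects and with more evaluable participants, and it grows under the Bonferroni correction if several tests are counted.

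**What to change.** In the section on analysis of fNIRS, EEG, and EMG data:

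1. For FcePDC, replace the change-score t-test with a linear model of the post-training value on arm and the pre-training value of the same measure. Report the adjusted arm difference with its 95% CI.
2. For C_W and L_W, replace the Mann-Whitney test with a rank-based ANCOVA: the ranked post value on arm and the ranked pre value. Fix this in advance rather than choosing a transformation after seeing the residuals. If Mann-Whitney is kept, state whether post values or changes are ranked.
3. Keep the Bonferroni correction already stated.
4. Wherever the correlation analysis selects on between-group differences in these measures, use the adjusted contrasts.

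The cost is wording and one degree of freedom per model. No new data, visits or participants are needed.

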#### Primary outcome measures

The primary outcome measure is the change in the FMA-UE scale score from baseline to the end of the 4-week intervention. The FMA-UE scale includes 33 items divided into four subscales (arm, wrist, hand, and coordination), each scored on a 3-point sequential scale [37]. Scoring is based on performing independent actions inside and outside the synergy pattern. The maximum score of 66 corresponds to undamaged motor function. The FMA-UE scale is often used to classify the severity of stroke injury, and the scale shows good reliability and validity. A FMA-UE score between 32 and 57 indicates moderate upper limb injury and an FMA-UE score between 58 and 65 indicates mild injury of the contralateral arm. FMA-UE sensation (0–12), passive range of motion, and pain (0–24) will also be assessed.

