#### Exploratory outcomes measures

The functional connection of the corticomuscular closed-loop network (CLN) in the resting and task states will be assessed. This mainly includes the extended partial directed coherence (FCePDC) value between the regions of interest (ROIs) and the small world measurement of the network, such as weighted clustering coefficient, weighted shortest path, and betweenness centrality.

EEG will be acquired according to the international 10–20 system. The Neuroscan system will be used to record the left and right sensorimotor and frontal-parietal cortex EEG. EEG is recorded from 32 Ag/AgCl scalp electrodes (sampling rate of 1000 Hz) using a BrainAmp DC amplifier and an anti-aliasing filter. The electrodes are designated Fz, F4, FC5, FC3, FC1, FCz, FC2, FC4, FC6, C5, C3, C1, Cz, C2, C4, C6, CP5, CP3, CP1, CPz, CP2, CP4, CP6, P3, POz, P4, POz, O1, O2, FCZ (reference), and AFZ (ground). The electrode impedance is kept below 10 kΩ. Some of the electrodes are located on the scalp in the central frontal lobe (FC3, FC4), centre (C3, C4, C5, C6), and the central parietal lobe (CP3, CP4).

EMG will be recorded from signals from the following muscles: the bilateral superior trapezius, anterior deltoid, posterior deltoid, middle deltoid, biceps brachii, triceps brachii, extensor carpi radialis, and flexor carpi radialis. The surface EMG signal will be recorded at 1500Hz through the Noraxon system using disposable Ag-AgCl electrodes with bipolar configuration, with a 2-cm distance between electrodes. After the standard skin preparation procedure, electrode pairs will be placed on each muscle’s abdomen, and the muscle’s surface EMG will be identified by palpation and a few blank tests of elbow flexion and extension. In addition, EMG signals will be monitored online before the experiment to evaluate the positioning and recording quality of the electrodes.

fNIRS uses a continuous wave optical system to measure oxygenated haemoglobin (HbO) in the cerebral cortex. The system’s light source generates near-infrared light (690 nm and 830 nm) at a fixed sampling rate of 10 Hz and a total of 95 channels. A 3D digitizer will be used to obtain the coordinates of the channel. These coordinates will be converted into the MNI coordinates, and then the NIRS_SPM toolbox will be used to project it onto the standard MNI brain model. With the above configuration, the channel can cover the SMA, the PMC, M1, the primary sensory cortex (S1), and the DLPFC.

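### The exploratory FcePDC comparisons use Bonferroni where Holm's procedure gives the same family-wise control and never rejects fewer hypotheses: a small optional gain

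*Protocol article*

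**What the plan says.** The section 'Analysis of fNIRS, EEG, and EMG data' sets out two sets of FcePDC tests. The first addresses "the average FcePDC value between the two groups in each frequency band before and after training": change from baseline is compared between arms by "an independent-sample two-tailed" *t*-test, one test per band. The second is a repeated-measures analysis of variance that compares FcePDC across directions of information flow, before and after training. The next sentence reads "Bonferroni correction is used to correct for multiple comparisons", and at the end of the paragraph α "is defined as 0.05". The number of bands, directions and contrasts is not given.

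These measures are listed under "Exploratory outcomes measures", where the plan also says: "The functional connection of the corticomuscular closed-loop network (CLN) in the resting and task states will be assessed". They are separate from the primary endpoint: "The primary outcome measure is the change in the FMA-UE scale score from baseline to the end of the 4-week intervention". The section 'Sample size estimation' sizes the trial on FMA-UE alone and claims no power for FcePDC.

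**The concern.** Bonferroni compares every p-value with α/m and keeps that divisor even after some hypotheses have been rejected. Holm's procedure relaxes the divisor step by step as hypotheses fall. It controls the same error rate under the same absence of assumptions, so for the p-value tests described here it is at least as good in every data set. The neural mechanism is a stated aim, the arms are small, and the change costs almost nothing. What is at stake is limited: some real FcePDC differences, in families where several effects are real, would be declared under Holm and missed under Bonferroni.

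**Working it through.** **No figure to reproduce.** The plan states no power and no number of comparisons for FcePDC. The check is therefore a short argument plus an illustration under stated assumptions.

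**Why Holm cannot do worse.** Order the p-values p(1) ≤ … ≤ p(m). Holm rejects p(1), p(2), … for as long as p(j) ≤ α/(m − j + 1). Since α/m ≤ α/(m − j + 1) at every step, any p-value that passes Bonferroni also passes Holm. At step 1 both thresholds equal α/m, so both methods make at least one rejection in exactly the same data sets.

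**Why Holm keeps the error rate.** Let m₀ hypotheses be truly null. The first true null to be rejected is reached after at most m − m₀ rejections, so its threshold is at most α/m₀. The union bound gives a family-wise error of at most m₀ × α/m₀ = α. No independence is used.

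**Inputs for the size.**
- From the document ('Sample size estimation'): 42 per arm and 20% dropout, so 42 × 0.8 = 33.6, taken as 33 per arm. Two-sided α = 0.05.
- Assumed: a standardised effect of 0.683 for each real contrast. This is the FMA-UE value; none is given for FcePDC.
- Assumed: m from 3 to 14 contrasts and correlation 0 or 0.5. The document gives neither.

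**Bonferroni power by formula** (normal approximation). The mean of the test statistic is 0.683 × √(33/2) = 2.774.
- m = 3: level 0.0167, critical value 2.394, power Φ(2.774 − 2.394) = 0.648.
- m = 10: level 0.005, critical value 2.807, power Φ(2.774 − 2.807) = 0.487.
- m = 14: level 0.00357, critical value 2.914, power Φ(2.774 − 2.914) = 0.445.

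**Bonferroni against Holm by simulation** (100,000 trials per setting, correlation 0.5):

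| Contrasts | Real | Average power, Bonferroni | Average power, Holm | Gain (points) | Any true finding, Bonferroni / Holm |
|---|---|---|---|---|---|
| 3 | 1 | 0.650 | 0.651 | 0.1 | 0.650 / 0.651 |
| 3 | 3 | 0.648 | 0.725 | 7.7 | 0.867 / 0.867 |
| 6 | 2 | 0.554 | 0.567 | 1.3 | 0.718 / 0.719 |
| 6 | 3 | 0.556 | 0.584 | 2.8 | 0.799 / 0.799 |
| 10 | 1 | 0.490 | 0.490 | 0.0 | 0.490 / 0.490 |
| 10 | 3 | 0.489 | 0.503 | 1.4 | 0.738 / 0.739 |
| 10 | 5 | 0.486 | 0.517 | 3.1 | 0.823 / 0.823 |
| 10 | 10 | 0.487 | 0.594 | 10.7 | 0.903 / 0.903 |
| 14 | 5 | 0.443 | 0.462 | 1.9 | 0.787 / 0.787 |
| 14 | 7 | 0.445 | 0.477 | 3.1 | 0.835 / 0.835 |
| 14 | 14 | 0.444 | 0.550 | 10.6 | 0.908 / 0.908 |

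Correlation 0 gives nearly the same gains (for example 3.2 points for 10 contrasts with 5 real, and 10.8 with all 10 real). With no real effect, the family-wise error was the same for both methods: 0.049 at correlation 0, and 0.037 to 0.044 at correlation 0.5.

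**The case against.** The strongest reply is that Bonferroni is pre-specified, valid under any dependence and errs only on the safe side. The family is exploratory, and no primary or secondary conclusion rests on it. All of that stands: this is a refinement, and the plan contains no error here.

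Four stronger readings are tempting, and the document does not support them.

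- *That power is given up for nothing.* Bonferroni yields simple simultaneous confidence intervals that match its tests, and Holm does not readily do so. With one real effect there is almost no power to regain.
- *That correlation between contrasts makes Bonferroni wrong.* Correlation only makes it conservative. The contrasts share participants and recordings, so positive correlation is plausible, but no value is given.
- *That a step-down max-T permutation of arm labels is the better replacement throughout.* It can gain more when correlation is high. In one simulation with 12 contrasts, 4 real, effect 0.683 and correlation 0.8, average power was 0.46 for Bonferroni, 0.47 for Holm and 0.60 for max-T. That rests on an assumed correlation of 0.8. The method also needs arm labels to be exchangeable under the null. It suits only the between-arm band contrasts, because the flow directions are tested by repeated-measures analysis of variance.
- *That real mechanism signals are lost before the correlation analysis.* The plan carries forward brain regions that differ significantly between groups, but it does not say that the Bonferroni-corrected FcePDC tests make that selection.

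It is also fair to say that the correction sentence directly follows the analysis-of-variance sentence, so its exact reach over the band tests is not fully clear.

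**Conclusion.** The point holds as an optional improvement of low weight. Holm's procedure dominates Bonferroni for the tests described, at the same 5% family-wise error and with no added assumption. Under the assumptions above, the gain in average power per contrast is 0 to 0.2 points with one real effect, about 1.5 to 3 with a third to a half real, and about 8 to 12 (typically 10) with all real. The chance of at least one true finding moves by no more than 0.2 points. These sizes depend on the unstated number of contrasts and of real effects, and on a borrowed effect size. The dominance itself depends on none of them. The FMA-UE result is not touched.

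**What to change.** Replace the Bonferroni sentence with: *Holm's step-down procedure is used to control the family-wise error at 5% across the FcePDC comparisons.* This covers both the between-arm band contrasts and the flow-direction comparisons. If the investigators can defend exchangeability of arm labels, step-down max-T permutation may be named as an alternative for the band contrasts only.

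The cost is one sentence and a few lines of code in MATLAB, which the trial already uses for its kinematic analysis. The drawback is that any simultaneous confidence intervals computed at Bonferroni width would no longer correspond exactly to the test decisions. If matching intervals matter more to the investigators than the modest gain, keeping Bonferroni is defensible.

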
Correlation analysis will also be employed. For the above brain functional features (based on brain imaging and graph theory analysis), brain regions with significant differences between groups are selected and relevant eigenvalues are extracted. The eigenvalues of functional brain connections of brain regions with significant differences or the partial and factor correlations between the eigenvalues of functional brain connections and upper limb scores are determined. Moreover, the factors that have the most significant impact on the cortex are analysed. The results are controlled for the influence of age, gender, education level, and other factors. Because the trial uses a single-blind design, the statisticians will conduct an interim analysis according to the label but without unblinding to guide the follow-up study.

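### The only tests stated for IFI, OFI and betweenness centrality are paired before/after t tests, which cannot attribute a change to Tai Chi; the ROI count and the scope of the Bonferroni correction also need settling

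*Protocol article*

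**What the plan says.** All of this stands in the protocol article, section Analysis of fNIRS, EEG, and EMG data, unless another section is named.

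- **Effective connectivity.** The plan says "the IFI and OFI values of ROI changes before and after training in the two groups are tested by paired two-tailed" t tests.
- **Betweenness centrality.** A paired t test "is used for the betweenness centrality parameter (BCX"). No other test is named for it.
- **Other neural measures.** The same paragraph compares the change in FcePDC between the two groups by an independent-sample t test. It compares the weighted clustering coefficient (C_W) and weighted shortest path length (L_W) between groups by the Mann-Whitney U test.
- **Regions of interest.** The plan says "Based on the above 14 ROIs, the inflow index (IFI) and the outflow index (OFI) are used to determine the causal relationship". The list before that sentence is: "the motor areas of the unaffected and affected sides are selected as ROIs, defined as Mu and Ma, respectively"; one somatosensory region for each side (Su, Sa); four frontal and parietal regions (Fu, FA, PAu, PAa); and two muscle regions on the affected side, proximal (PM) and distal (DM).
- **Multiplicity.** One sentence states a Bonferroni correction. It follows the repeated measures ANOVA of FcePDC and precedes the tests for C_W, L_W, IFI, OFI and BCX. It does not say which tests it covers. Alpha is 0.05.
- **Status.** The corticomuscular network measures are listed under Exploratory outcomes measures.

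**The concern.** A paired t test compares a participant with himself or herself. It cannot compare two independent randomised arms, so the sentence can only mean a before/after test inside each arm. Such a test asks whether an arm changed. The mechanism question is whether the Tai Chi arm changed by a different amount from the control arm.

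The distinction matters in this trial. Both arms receive the same routine care, health education and 20 one-hour rehabilitation sessions (Intervention), and participants enter 2 weeks to 6 months after a first stroke (Inclusion criteria). Change in both arms is plausible with no Tai Chi effect at all. A pair of within-arm results, one significant and one not, is easily read as a treatment effect although the difference has not been tested.

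Two further points leave the same analysis loosely defined. The number of regions does not match the list, so the set of tests is not fixed. The scope of the Bonferroni correction is open, so the threshold for these tests is not fixed either.

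**Working it through.** **1. Region count.** Motor 2 (Mu, Ma) + somatosensory 2 (Su, Sa) + frontal and parietal 4 (Fu, FA, PAu, PAa) + muscle 2 (PM, DM) = 10. The stated figure of 14 is not reproduced. Adding unaffected-side counterparts of PM and DM would give 12, still not 14.

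**2. How often paired tests mislead when the arms do not differ.**

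Inputs: n = 42 per arm (Sample size estimation); two-sided alpha 0.05. The true change, divided by the SD of change and called dz, is taken as equal in both arms. The document gives no value for it, so dz is assumed and shown over 0.2 to 0.5.

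- Probability that one arm's paired test is significant: p = P(|T| > 2.02), where T is noncentral t with 41 degrees of freedom and noncentrality dz × √42.
- The arms are independent, so P(significant in Tai Chi, not in control) = p(1 − p).

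| dz (assumed) | dz × √42 | p | p(1 − p) |
|---|---|---|---|
| 0.2 | 1.30 | 0.244 | 0.244 × 0.756 = 0.185 |
| 0.3 | 1.94 | 0.476 | 0.476 × 0.524 = 0.249 |
| 0.4 | 2.59 | 0.716 | 0.716 × 0.284 = 0.203 |
| 0.5 | 3.24 | 0.886 | 0.886 × 0.114 = 0.101 |

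The range is 10% to 25% per measure. The product p(1 − p) cannot exceed 25%, so the upper end is its ceiling. With 34 per arm (42 × 0.8 = 33.6, using the protocol's 20% dropout) the four values are 16%, 24%, 24% and 16%. A two-sided 5% between-arm test of the change would favour Tai Chi wrongly in 2.5% of trials, whatever the common change.

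**3. What the open count and scope do to the threshold.** Assume one frequency band and one task, and count only IFI and OFI, each tested once per region between arms:

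- 10 regions: 10 × 2 = 20 tests, 0.05/20 = 0.0025.
- 14 regions: 14 × 2 = 28 tests, 0.05/28 = 0.0018.
- Not covered by the correction: 0.05 per test.

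These are illustrations of the ambiguity. The real family also depends on BCX, frequency bands, tasks, hands and the resting state.

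**The case against.** Several stronger readings are tempting, and the document does not support them.

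- *No neural change could be attributed to Tai Chi.* Not so: FcePDC change, C_W and L_W each have a between-group test. The problem is confined to IFI, OFI and BCX.
- *There is no multiplicity correction.* A Bonferroni correction is stated in general words. Its place in the paragraph makes its scope unclear, not absent.
- *The wrong number of regions makes the correction wrong.* The plan never uses 14 as a divisor. The mismatch has no bearing on attribution to Tai Chi either; it leaves the analysis set undefined.
- *The correlation step ignores randomised group.* Its covariate list ends with other, unnamed factors, and it does not say that the arms are pooled. An article may leave the full list to the analysis plan.

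The best defence of the paired tests has three parts. First, the plan never says it will infer a Tai Chi effect from one arm being significant and the other not. That is true, so the 10% to 25% describes a likely misreading and not a stated decision rule. Second, the correlation step says "brain regions with significant differences between groups are selected and relevant eigenvalues are extracted", which implies some between-group comparison of regional features. That is fair, but no such test is named for IFI, OFI or BCX, and the only tests that are named point the other way. Third, a mixed model with a group × time interaction is planned. It stands under the heading for behavioural indicators, while the neural section names its own tests.

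Finally, these are exploratory outcomes. That lowers the importance of the point but does not make a within-arm test answer a between-arm question.

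**Conclusion.** The point holds for three exploratory measures. As written, the tests stated for IFI, OFI and BCX cannot separate a Tai Chi effect from recovery or rehabilitation shared by both arms. The 10% to 25% figure rests on an assumed equal standardised change of 0.2 to 0.5, on 42 analysed per arm, and on a reader treating discordant within-arm results as an effect.

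The count of 14 against 10 named regions is a plain contradiction in the text. The Bonferroni scope is an ambiguity. Neither touches the primary FMA-UE analysis or the between-group tests of FcePDC, C_W and L_W. The correction is worth making because the neural mechanism is a declared aim of the trial, and the plan already contains the right method for a neighbouring measure.

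**What to change.** 1. For IFI, OFI and BCX, compare the change from the pre-training value between arms by the independent-sample t test already planned for FcePDC, or by ANCOVA with the pre-training value as covariate. Keep within-arm changes as description only.
2. Reconcile the region count with the list: either correct 14 to the 10 named or define the other four.
3. State that the Bonferroni correction covers the IFI, OFI and BCX tests, and say how regions, frequency bands and tasks enter the family.

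The cost is a change of wording, with no new data, visits or participants. The downside is small: a stricter threshold for exploratory results, and a between-arm contrast that is less precise than a change within one arm (with equal SDs, variance 2σ²/n against σ²/n).
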